# Mobile phone text messaging plus motivational interviewing versus usual care: study protocol for a randomized controlled trial to evaluate effects on breastfeeding, child health, and survival outcomes, among women living with HIV (MTI-MI)

**DOI:** 10.1186/s13063-023-07647-9

**Published:** 2023-10-05

**Keywords:** Breastfeeding, HIV/AIDS, Mobile phone text messaging, Motivational interviewing

## Abstract

**Background:**

Many infants in low-resourced settings at high risk of infectious disease morbidity and death are deprived of the immunological and nutritional benefits of breast milk, through an attenuated duration of breast milk exposure. South Africa has one of the lowest exclusive breastfeeding rates in Africa, with 8% of infants under 6 months of age. We assume that breastfeeding is sustained among women living with HIV receiving weekly text messages and motivational interviewing and that this contributes to improved infant health outcomes.

**Objectives:**

(1) To evaluate the effectiveness of a combined intervention of mobile phone text messaging and motivational interviewing in promoting (a) exclusive breastfeeding and (b) any form of breastfeeding, until 6 months of child age, compared to usual care, among mothers living with HIV. (2) To evaluate the effectiveness of a combined intervention on (a) reduction in all-cause hospitalization and mortality rates and (b) improvements in infant linear growth, compared to usual care, among HIV-exposed infants aged 0–6 months.

**Methods:**

We are conducting a clinical trial to determine whether text messaging plus motivational interviewing prolongs breastfeeding and improves infant health outcomes. We are recruiting 275 women living with HIV and their HIV-exposed infants at birth and randomly assign study interventions for 6 months.

**Statistical methods:**

Breastfeeding rates are compared between the study groups using a standard proportion test and binomial regression. Survival endpoints are presented using Kaplan–Meier survival curves and compared between the study groups using the Cox proportional-hazards regression model. The count endpoint is analysed using the Poisson random-effects model and mean cumulative function. We use mixed linear regression models to assess the evolution of infant growth over time. The maximum likelihood method will be used to handle missing data.

**Discussion:**

The study findings may facilitate decision-making on (1) whether implementation of the breastfeeding policy achieved the desired outcomes, (2) interventions needed to sustain breastfeeding, and (3) whether the interventions do have an impact on child health.

**Trial registration:**

ClinicalTrials.gov NCT05063240. Pan African Clinical Trial Registry PACTR202110870407786. Oct. 1, 2021.

**Supplementary Information:**

The online version contains supplementary material available at 10.1186/s13063-023-07647-9.

## Background

Despite a consistently high antenatal human immunodeficiency virus (HIV) prevalence of about 30%, South Africa has made remarkable progress in reducing the risk of vertical transmission of HIV during the first 2 months of life, from 23% in 2003 to 0.7% in 2019 [1]. In 2016, data was published indicating the rate of cumulative vertical transmission by the age of 18 months to be at 4.3% [1]. This success is largely attributed to the adoption of the “Option B + ” strategy into policy, where mothers living with HIV receive combination antiretroviral treatment (cART), irrespective of CD4 count or clinical disease severity, to be maintained either for the duration of breastfeeding or as lifelong treatment [2, 3]. Over 90% of women living with HIV are on ART [1]. Given the benefits of breastfeeding and risks of not breastfeeding, mothers need to be supported to breastfeed their infants, while maintaining virological suppression to minimize vertical transmission risk [1]. With increased access to ART in South Africa, the national infant feeding guidelines are now the same for mothers living with and without HIV [4]. The guidelines endorse exclusive breastfeeding for the first 6 months, followed by appropriate complementary foods and continued breastfeeding for 2 years or longer [1].

Irrespective of HIV exposure, South African infants still experience high rates of morbidity and mortality [5]. South Africa’s under-five child mortality declined between 2003 and 2015, largely due to declining paediatric HIV infections and increasing availability of paediatric cART [5, 6]. South Africa’s under-five mortality rate in 2021 was at 30.8 per 1000 live births [7], double that of countries with similar-sized economies and health expenditures. HIV-exposed uninfected (HEU) children have more deaths and morbidity during infancy due to common childhood infections than HIV-unexposed infants [8, 9]. Considering the South African HIV-exposed infant population size, even a moderate additional increase in morbidity adds to the burden on the public healthcare system.

The evidence indicates that the benefits of breastfeeding outweigh the risks of not breastfeeding, regardless of the maternal HIV status [10, 11]. Breastfeeding protects against childhood mortality from diarrhoea disease and respiratory tract infections regardless of maternal HIV status [10–12]. Universal coverage with exclusive breastfeeding for 6 months and continued breastfeeding up to 1 year may prevent 13% of under-five deaths in countries with a high HIV prevalence and high under-five mortality rate [13]. Lack of breastfeeding doubles the risk of infant death in the first 6 months of life [14]. Many infants in low-resourced settings at high risk of infectious disease morbidity and death are deprived of the immunological and nutritional benefits of breast milk [15], through less breast milk exposure possibly due to efforts to reduce postnatal HIV transmission through breast milk [15, 16]. South Africa has one of the lowest exclusive breastfeeding rates in Africa, between 8 and 32% in infants under 6 months of age [10, 17, 18]. Innovative strategies are needed to encourage breastfeeding as a primary strategy for child survival [1].

The need for innovative strategies to support breastfeeding in resource-limited settings is increasingly pertinent in view of the increased disease burden on the stressed public healthcare system [1]. Interventions such as antenatal education, lactation counselling, peer counsellor support, telephonic support, and group counselling improve optimal breastfeeding practices [19]. Counselling or education delivered concurrently has a higher impact on breastfeeding rates than interventions delivered independently [19].

Patient-centred approaches for negotiating behaviour change outperform approaches that instruct patients to change behaviour through providing advice [20]. Mobile phone text messaging, a simple, low-cost intervention, improves medication adherence among patients with HIV, diabetes, and tuberculosis [21–23]. Motivational interviewing, a patient-centred non-coercive approach that explores patient readiness to change behaviour and supports the person’s commitment to do so in the preferred direction [24, 25], has been beneficial across many health problems, including HIV viral load suppression, weight loss, and alcohol and tobacco use, and medication adherence among patients with HIV and tuberculosis. Combining a number of intervention approaches is more likely to influence behaviour change than an individual approach [26].

We initiated a usual care-controlled randomized trial evaluating the effects of interactive weekly mobile phone text messaging plus motivational interviewing on sustaining breastfeeding and improving child health and survival, among mothers living with HIV. The study is an extension of our pilot study that tested the feasibility of the large trial. This group comprises 17.9% of the antenatal population in the Western Cape province, South Africa, where the majority stopped breastfeeding early [16].

## Objectives and hypotheses

The trial is primarily evaluating the effects of a combined intervention of interactive weekly mobile phone text messaging plus motivational interviewing in promoting (a) exclusive breastfeeding and (b) any form of breastfeeding, until 6 months of child age, compared to usual care, among mothers living with HIV. Secondarily, to compare the effects of the combined intervention in improving infant health outcomes, including (a) reduction in all-cause hospitalization and mortality rates and (b) improvement in infant linear growth, compared to usual care, among HIV-exposed infants aged 0–6 months. We hypothesize that breastfeeding will be sustained among mothers living with HIV receiving the combined intervention and that this will contribute to improved infant health outcomes.

## Study methods and design

### Trial design

A parallel group, adaptive [27], usual care-controlled randomized superiority trial evaluating infant feeding practices at four time points among 275 mother-infant pairs who are randomly assigned mobile phone text messaging plus motivational interviewing and usual care for 24 weeks. The fixed randomization allocation sequence was generated using blocks of different sizes, with a 1:1 allocation ratio. This trial protocol was written following the Standard Protocol Items Recommendations for Interventional Trials (SPIRIT) guidelines [28].

### Study setting

The Western Cape has a population of six million people, more than 85% rely on public health sector services and approximately 95,000 pregnant women are seen annually in public antenatal care clinics [29]. Among pregnant women living with HIV, more than 70% know their HIV-positive status before pregnancy and an estimated 90% are already on ART before pregnancy. Women receive infant feeding counselling in groups during antenatal and postnatal clinic visits. Exclusive breastfeeding at age 6 months is very low (~ 8%) [17]. Women from peri-urban informal and formal settlements are invited to participate within 24 h of giving birth at Khayelitsha District Hospital and followed for 6 months at Masiphuhlisane Research Centre in Khayelitsha.

### Eligibility criteria

Mothers living with HIV, giving birth at Khayelitsha District Hospital, are eligible if they initiate breastfeeding within 24 h of giving birth, on cART, 18 years or older, own a mobile phone, and their infants are discharged after delivery. Mothers are excluded if they initiate formula feeding within 24 h of giving birth, give birth to more than one infant, infant birthweight is < 2500 g, or gestational age is < 36 weeks. Multiple births and low birthweight are associated with suboptimal infant feeding practices and poor infant health outcomes.

### Study interventions

Irrespective of study group assignment, participants receive health services according to provincial guidelines applicable in the sector during the study. Participants are evaluated soon after giving birth and post-delivery until 24 weeks post-randomization. There are no special criteria for discontinuing or modifying allocated interventions.

### Mobile phone text messaging and motivational interviewing

Every Monday morning, a research assistant sends a text message to mothers in the intervention group, encouraging them to exclusively breastfeed and inquiring if they have any problems with breastfeeding. Mothers are requested to respond by text within 48 h, indicating whether she has a problem with breastfeeding. The research assistant contacts mothers who either indicate a breastfeeding problem or fail to respond within 48 h. Mothers have individual motivational interviews post-delivery at weeks 2, 6, and 10. During the interviews, the research assistant and the mother discuss problems with breastfeeding and potential solutions, reinforce mother’s own self-motivational statements and readiness to change, and affirm the mother’s freedom of choice. Text messaging and motivational interview are discontinued for mothers who completely stop breastfeeding but are followed until the end of the study. As soon as the mother stops breastfeeding completely, the mother-infant pair will have achieved the co-primary outcomes but will still be followed for the secondary outcomes.

### Usual care infant feeding counselling

Participants in the usual care group are counselled by primary healthcare nurses and trained lay counsellors to exclusively breastfeed for the first six months as part of routine healthcare.

### Exposure variables

Nuisance exposure variables of no primary interest: (1) timing of cART initiation: classified as prior to conception or during pregnancy according to the mother self-report or abstracted from the maternity case record; (2) viral load at delivery; (3) CD4 count at delivery; and (4) infant HIV infection status: all infant diagnostic HIV-PCR tests are performed by the national health laboratory system (NHLS). Infants are retrospectively classified at 6 months of age as HEU if there is no evidence of infant HIV infection in the NHLS database or as HIV infected; mother’s HIV disclosure status: classified as yes or no according to mother self-report; baseline socio-demographic characteristic obtained by interviewing the mother at study entry.

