### Safety events

Safety events are collected from the time the participant consents to trial participation until the participant is discharged from the trial or at the trial conclusion. Potential social unintended consequences of safety events include relationship conflicts with partners due to study participation; reduced child monitoring due to exaggerated perception of the benefits of breastfeeding (assess infant immunization history as proxy), psychological stress, or guilt due to non-compliance with exclusive breastfeeding; and inadvertent disclosure of participant’s HIV status.

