### Sample size, power, and detectable differences

We expect an exclusive breastfeeding rate of 8% at age 6 months in the usual care group [17]. We want to detect a difference of 15% between the intervention and usual care groups (i.e., 23% vs 8%). The traditional fixed sample size computations using WinPepi give a sample size of 182 for a two-sided test. Using inflation factor 1.01 for two planned analyses of O’Brien-Fleming boundaries at the 0.05 significance level and 80% power, we compute the maximum sample size of 182 × 1.01 = 184. The sample size is inflated by 33% to 275, to account for loss to follow-up (30%) and infants who test HIV positive (3%) who are included in the analysis ignoring infant HIV status and repeat the analysis excluding HIV-infected infants. The study is not powered for the co-primary endpoint (i.e., any form of breastfeeding rate at 6 months of age) and secondary endpoints. The co-primary and secondary endpoint analyses are considered exploratory and may only be supportive of the primary analysis of exclusive breastfeeding endpoint. No adjustment to the significance level for testing of multiple co-primary endpoints is made since all the co-primary endpoint analyses are considered exploratory.

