**Assessment**						
Demographics	x					
Baseline data	x					
Anthropometrics		x	x	x	x	
Maternal NHLS antenatal CD4 count and viral load	x					
NHLS infant HIV-PCR result				x	x	
Infant feeding questionnaire		x	x	x	x	
Health questionnaire including medications (e.g. immunization, morbidity and mortality, infant weight, and height measurements)		x	x	x	x	
Health record reviews—hospital electronic administration systems: infant hospitalization and mortality					x	

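### Infant HIV infection is treated as a nuisance exposure and untested infants are coded uninfected; it should be reported by arm as a safety outcome with a not-tested class

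*Protocol article*

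**What the plan says.** All references are to the protocol article.

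- **Exposure variables.** Infant HIV infection status is item 4 under "Nuisance exposure variables of no primary interest", next to timing of cART initiation and maternal viral load and CD4 count at delivery. Classification is late ("Infants are retrospectively classified at 6 months of age") and has only two outcomes. An infant is entered "as HEU if there is no evidence of infant HIV infection in the NHLS database"; the sole alternative is the infected class. There is no class for an infant without a test.
- **Sample size, power, and detectable differences.** The inflation allows for "infants who test HIV positive (3%) who are included in the analysis ignoring infant HIV status and repeat the analysis excluding HIV-infected infants".
- **Safety events.** The events named are social or psychological: "Potential social unintended consequences of safety events include relationship conflicts with partners", reduced child monitoring, stress or guilt, and disclosure of the mother's status. Infant infection is not among them.
- **Objectives, Endpoint variables, Table 2, Planned schedule of interim analysis.** Infant infection is not an objective, an endpoint or a named item of the interim comparison between arms.
- **Table 1, Assessment.** The row "NHLS infant HIV-PCR result" is marked at the week-10 and week-24 visits, so the results are already being retrieved.
- **Background.** The text accepts that breastfeeding by mothers living with HIV carries a transmission risk to be kept low by viral suppression.

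**The concern.** The other HIV-related items in the nuisance list are settled by delivery, at about the time of randomisation. Infant HIV status is not. It is read at 6 months, after the whole intervention period, and the intervention aims to make breastfeeding more exclusive and longer. On the article's own account of transmission, infection after birth is a possible consequence of allocation. It should be treated as an outcome.

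Three things follow.

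1. With only two classes, missing information becomes a favourable result, so recorded infection can only be biased downward by non-testing.
2. Removing infants by their 6-month status means that the groups compared in the repeat analysis are no longer those formed by randomisation, if allocation affects infection.
3. Because infection is not named as an outcome, nothing in the article commits the trial to showing it by arm. A reader of a breastfeeding trial in this population will look for that table.

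**Working it through.** **The plan's own figures.** Pooled-variance test of 8% versus 23%, two-sided 0.05, 80% power, no continuity correction: 91 per arm, 182 in total. 182 × 1.01 = 183.8, taken as 184. 184 / (1 − 0.33) = 274.6, taken as 275. The sample size reproduces and is not in dispute.

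**Expected infections.** 275 × 0.03 = 8.25, about 4 per arm under 1:1 allocation.

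**Effect of coding untested infants as uninfected.** The documents do not give the untested share *u*, so it is varied here. If untested infants have the same true risk as tested ones, recorded rate = true rate × (1 − *u*).

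| *u* | Recorded rate if true rate is 3.0% | Recorded cases of 275 |
|---|---|---|
| 0% | 3.0% | 8.3 |
| 10% | 2.7% | 7.4 |
| 20% | 2.4% | 6.6 |
| 30% | 2.1% | 5.8 |

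**Effect on the comparison.** Illustrative true rates are 3% (usual care) and 6% (intervention), a risk ratio of 2.0 and a difference of 3.0 points.

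- 30% untested in both arms: difference = 0.70 × 3.0 = 2.1 points; ratio unchanged.
- 10% untested in usual care, 30% in intervention: (0.06 × 0.70) / (0.03 × 0.90) = 0.042 / 0.027 = 1.56.
- 30% untested in usual care, 10% in intervention: (0.06 × 0.90) / (0.03 × 0.70) = 0.054 / 0.021 = 2.57.

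Equal non-testing shrinks the difference. Unequal non-testing can move the ratio either way.

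**The repeat analysis.** Under the two-class rule, an infected infant with no test on file is coded HEU and stays in. The analysis therefore conditions on a post-randomisation variable and also does not reliably exclude the infants it sets out to exclude.

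**What a comparison by arm could show.** With 137 per arm, Fisher's exact test has about 13% power for 3% versus 6% and 45% for 3% versus 9%. By the normal approximation, 80% power for 3% versus 6% needs 749 per arm. As a purely hypothetical split of 8 infections, 6/138 − 2/137 = 4.3% − 1.5% = +2.9 points (unrounded), with a Newcombe 95% interval of −1.5 to +7.8.

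**The case against.** A reader might infer that harm would be concealed: infections never tabulated, and infected infants taken out of the infant-health results. The documents do not support that.

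- Infected infants stay in the first analysis. Exclusion applies only to the repeat, which is described in the section on sample size for exclusive breastfeeding. No exclusion is stated for the hospitalisation and death endpoints.
- The list under Safety events is open and describes social consequences. Safety analyses promises summaries by study group. Trial safety monitoring gives the DSMB unblinded safety data, a judgement of relatedness and the power to suspend the trial without a preset rule. An article may leave the full adverse-event definition to the full protocol.
- It is tempting to equate the 30% loss to follow-up with 30% untested. Status comes from the national laboratory database, not from attendance, and Recruitment and retention seeks continued record access after withdrawal. So 30% is only the upper end of an illustration.
- A reader might also infer that models will adjust for 6-month infant status. The section on exploratory analyses of primary endpoints speaks of baseline variables, so such adjustment is not clearly planned.
- The 3% is not divided into infection present at birth and later infection, and only the latter could respond to the intervention. Mothers must be on cART to enrol, and usual care also counsels exclusive breastfeeding. The text acknowledges transmission risk but does not rank it as the main hazard.

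These points limit the concern without removing it. The nuisance label, the default to uninfected and the exclusion are all in the current text. DSMB review would capture infections systematically only if they are recorded as safety events, which the article does not say.

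**Conclusion.** The point holds in a limited form. A post-randomisation outcome that the intervention might affect is labelled a nuisance exposure. Its classification rule biases recorded infection downward when tests are missing, and the repeat analysis conditions on it. Infection is not named as an endpoint or safety event, and no comparison between arms is stated.

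The size depends on an unknown. For 0 to 30% untested, assuming equal risk in tested and untested infants, a true 3.0% reads as 3.0% to 2.1%. If testing differs by arm, a true ratio of 2.0 could read as 1.56 or 2.57 under the illustrative shares used. The confirmatory test of exclusive breastfeeding and the sample size are unaffected. What is at stake is the completeness and accuracy of the safety account.

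**What to change.** 1. Move infant HIV infection from the nuisance list to the safety outcomes. Report the number infected by randomised arm, with an exact confidence interval, to the DSMB and in the results.
2. Replace the two-class rule with three classes: infected; tested negative, with age at last negative test; and not tested. Give counts by arm. Do not take a negative result at week 10 as proof of status at 24 weeks, since it says nothing about the interval between.
3. Keep the analysis of all infants as the main one. Label the analysis without infected infants as descriptive and conditioned on a post-randomisation variable.

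The cost is wording in the plan and one additional safety table. The PCR results are already retrieved at weeks 10 and 24, so no further participants, visits or tests are needed. The drawback is imprecision: about 8 infections give wide intervals, and the report should say that the comparison is descriptive and that finding no difference is not evidence of no excess.
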